### Strengths of the protocol

The present single-center, open-label, intraindividual trial will be carried out as soon as regulatory approvals have been obtained and will take place over three years at Poitiers Hospital, starting in winter 2026.

The literature is mostly composed of retrospective studies with potential selection bias due to the inclusion of patients who tested positive for a pathogen with the reference method [5,14]. Moreover, the sample sizes were often limited, as were the pathogens sought. The assessment of patients' pain and comfort was often neglected. The main strengths of our protocol compared to this literature are its focus on infants under 2 years of age, a population for which high-quality sampling is difficult to achieve. We propose a prospective crossover design in a clinical setting that enables a reliable performance comparison between the two procedures, limiting biases. If the primary objective is fulfilled, saliva sampling may be considered the first-line sample for respiratory diagnostics in children under 2 years in our hospital.

### Limitations of the protocol

The primary outcome is the overall agreement between the two tests. The primary outcome will be affected by the microbial epidemiology of respiratory infections, which may vary each year. Even if some tendencies can be predicted in seasonality, the emergence of a new viral lineage or variant may occur [1,15]. The proportion of atypical bacteria, such as *Mycoplasma pneumoniae* and *Chlamydophila pneumoniae*, is also unpredictable, as they are known to cause epidemics every 5 to 7 years (16). This issue could be partially addressed by the 3-year study design, which will limit the impact of epidemiologic variations.

The required sample size was calculated according to this primary outcome, whose agreement can be inflated by many double-negative samples. The other results, i.e., discordant and double-positive samples, will be important to consider to better appraise the usefulness of saliva-based tests. Nevertheless, the related confidence intervals could be large.

The single-center study design may also affect the findings, as the standard of care and procedures may vary from those of other hospitals. This study should be considered a pilot study and, if the primary endpoint is achieved, will be followed by a randomized, multicenter national study for definitive validation of the use of saliva sampling in children with bronchiolitis or respiratory symptoms in pediatric departments.

Some patients may be excluded from the study if one of the two samples cannot be obtained or analyzed (e.g., if the volume is too low for analysis). A 10% loss of samples has already been considered when determining the sample size to address this issue. Moreover, the saliva sponge swab that will be used in this protocol has already been widely used in several studies and has proven successful in recovering enough saliva for further analyses.

Our study aims to evaluate the opportunity to replace NPA, the current reference approach in clinical practice, by saliva sampling. Importantly, NPA does not represent an absolute gold standard.

Randomization will determine the order in which the two procedures (saliva sampling and NPA) are performed. The interaction effect of the order will be tested in statistical analyses, particularly for criteria relating to the time taken to perform the procedure and the level of pain or satisfaction (secondary outcomes). For reasons of feasibility and ethics, we cannot plan a washout period long enough to prevent this type of interaction. In the event of a significant interaction, the results may be presented conditional on the first sampling.

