**Value of the Protocol**	Most studies were retrospective. This proposal is the first to prospectively evaluate the feasibility and performance of saliva sampling for the etiological diagnosis of respiratory distress in children under the age of two. Randomizing the order of the sampling techniques will help reduce bias due to confounders, even if the first sample could influence the quality of the second. If diagnostic concordance with nasopharyngeal aspirate (NPA) is demonstrated, this method could offer a noninvasive and better-tolerated alternative, with several potential advantages: - For the child and their family: reduced pain, reduced parental stress. - For caregivers: reduced risk of splashing or contact with nasal secretions, greater acceptability of the procedure. - For healthcare organizations: speed, simplicity, and the possibility of use outside the hospital (community medicine, nurseries, population screening).

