## Description of protocol

### Study design

The PreSap study is a publicly funded, national, prospective, monocentric, randomized clinical trial comparing saliva samples and NPA in children between 28 days and 2 years old (Fig. 1). Once the protocol has been explained to the parents and child, and their agreement has been received, all patients will undergo the two sampling procedures after a randomization determining the order (crossover design with a 1:1 ratio). Randomization will be carried out with the REDCap software. Depending on the randomization, the saliva sample will be taken first or second, and the same will be done for the NPA. A rest period will be allowed between each sample so that the child can be calm again for the second sample. All temporal and behavioral data will be recorded.

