**Table utbl0002:** 

Effective (proportion)		Saliva-based test		Total
		Positive result	Negative result	
NPA-based test	Positive result	()	()	()
	Negative result	()	()	()
	Total	()	()	()

*Analysis of the secondary outcomes (a).* For each pathogen, the following estimations and related 95%CI will also be estimated with the use of NPA-based results as gold standards [13]. The positive and negative percent agreement are respectively equaled to and . The Cohen’s kappa coefficient is, where . Additionally, by considering the NPA-based as the reference, sensitivity and specificity are .and, respectively. In addition, positive and negative predictive values are and, respectively.

*Secondary outcomes (b-d).* The pain level, the parental satisfaction, and the time spent by caregivers will be compared according to the sampling technique (NPA versus Saliva) in terms of means by paired two-sample t-tests. The interaction with the order (saliva/NPA or NPA/saliva) will also be explored by mixed linear models.

*Secondary outcomes (e-g).* The causes of complications, procedural discrepancies, and non-conclusive results will be described in terms of frequencies and percentages. In addition, to compare the two techniques, the following three proportions will be estimated and compared by using McNemar test: i) the proportion of sampling with at least one event among the following complications: bleeding, irritation, and exposure of healthcare workers to biological agents; ii) the proportion of sampling which has necessitated multiple healthcare workers, repeated procedure, or cessation of care by the legal representative; iii) the proportion of interventions with non-conclusive results: insufficient sample volume, refusal of sampling, or laboratory measurement errors. The interaction with the order (saliva/NPA or NPA/saliva) will also be explored by mixed logistic models.

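### A significant technique-by-order interaction is the wrong condition for presenting the comfort outcomes by first sampling: it measures period plus summed carry-over, not the bias of the paired comparison

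*Protocol article*

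**What the plan says.** Under Study design, every child has both samplings, in one of two orders randomised 1:1, with only a pause in between: "A rest period will be allowed between each sample so that the child can be calm again for the second sample". The Specifications table (Value of the Protocol) concedes that randomising the order helps "even if the first sample could influence the quality of the second".

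Under Data analysis, pain, parental satisfaction and caregiver time are compared "in terms of means by paired two-sample t-tests", and then: "The interaction with the order (saliva/NPA or NPA/saliva) will also be explored by mixed linear models". Complications, procedural discrepancies and non-conclusive results are compared by McNemar tests, followed by the same exploration on the logit scale: "The interaction with the order (saliva/NPA or NPA/saliva) will also be explored by mixed logistic models".

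The Limitations section returns to this interaction, mainly for time, pain and satisfaction. It explains that "we cannot plan a washout period long enough to prevent this type of interaction" and concludes: "In the event of a significant interaction, the results may be presented conditional on the first sampling".

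**The concern.** The Limitations section reads the interaction as carry-over that a longer washout would have prevented, and makes its significance the occasion for a different presentation of results. In a design with two techniques and two orders, the technique-by-order term is the same column as first versus second position. A general second-position effect, such as tiredness or residual distress in an infant, enters it in full, and that effect cancels in the paired comparison. The quantity that does bias the paired comparison is the difference between the two carry-overs, and it is not in this term.

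At stake is how the estimates for tolerance and comfort are reported. A test of the wrong contrast could prompt a change of presentation when the paired result is unbiased. It could also give reassurance when the paired result is not. Because the presentation is both optional and dependent on the data, it leaves room for selective reporting.

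**Working it through.** **Inputs.** The two orders, the 1:1 allocation, the paired t-tests and the interaction models come from Study design and Data analysis. The article gives no figure for the interaction test, and no SD or within-child correlation for pain, satisfaction or time, so those values are assumed below.

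**The plan's own sample size.** 1.96² × 0.95 × 0.05 / 0.02² = 456.2, which rounds up to the stated 457. Adding 10% gives 457 × 1.10 = 502.7, against the stated 502. After a 10% loss from 502, 451.8 remain, or about 226 per order.

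**Algebra.** Let T be the true NPA-minus-saliva difference, P the effect of being second, Ls the carry-over of saliva onto NPA, and Ln that of NPA onto saliva.

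- Saliva first: NPA − saliva = T + P + Ls
- NPA first: NPA − saliva = T − P − Ln
- Difference between orders (the planned interaction): 2P + Ls + Ln
- Mean over both orders (the paired estimate): T + (Ls − Ln)/2
- Difference between orders in the child's average score (the order main effect): (Ls − Ln)/2, which is exactly the bias

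The column identity also holds in the logistic models; the additive bias formula is for the linear ones.

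**Numbers** (assumed: SD 4, correlation 0.5, 226 per order, T = 2.0, two-sided 5%). The SD of the within-child difference is 4 × √(2 × 0.5) = 4. The SE of the interaction contrast is 4 × √(2/226) = 0.376.

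- P = 0.5, no carry-over: contrast 1.0, and 1.0/0.376 = 2.66, so the power is Φ(2.66 − 1.96) ≈ 0.76. Bias 0; the paired estimate is 2.0.
- Ln = 1, no period effect: the contrast is again 1.0 and the power again about 0.76, but the bias is −0.5 and the paired estimate is 1.5.
- Ln = 1 with P = −0.5: contrast 0, significant in 5%, bias still −0.5.

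The first two cases cannot be told apart by the test, yet one is unbiased and the other is not.

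**What the alternative presentation would show.** If it means results by order, the first case gives 2.0 + 0.5 = 2.5 and 2.0 − 0.5 = 1.5; neither is T. If it means first samples only, the comparison is free of carry-over but unpaired. Its SE is 4 × √(2/226) = 0.38, against 4/√452 = 0.19 for the paired comparison. The ratio is √(2/(1 − ρ)): 1.7, 2.0 and 2.6 at correlations of 0.3, 0.5 and 0.7.

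**Simulation check** (457 children, 1:1 orders, correlation 0.5, no true technique effect, 4,000 runs per row, effects in SD units):

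| P | Ls | Ln | Interaction significant | Bias of paired estimate |
|---|---|---|---|---|
| 0.1 | 0 | 0 | 58% | 0.00 |
| 0.2 | 0 | 0 | 99% | 0.00 |
| 0 | 0.2 | 0.2 | 99% | 0.00 |
| 0 | 0 | 0.2 | 57% | −0.10 |
| −0.1 | 0 | 0.2 | 5% | −0.10 |
| 0 | 0.2 | −0.2 | 5% | +0.20 |

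Testing the order main effect instead would not be a good gatekeeper either. In the fourth row it was significant in only about 24% of runs.

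**The case against.** Several points on the other side are right and limit the finding.

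- **The test does respond to carry-over.** One might infer that the interaction is purely a period effect and blind to carry-over. It is not: one-way carry-over of 0.2 or 0.3 SD alone makes it significant in 57% or 89% of runs. The washout sentence is not false either, since a longer washout would remove Ls + Ln from the contrast. What the test cannot do is separate carry-over from period, or show the difference Ls − Ln.
- **No replacement rule is stated.** One might infer that a significant interaction replaces the paired result. The wording is permissive, and nothing says the paired comparison is withdrawn. The significance condition itself is nonetheless stated.
- **The fully hidden bias needs exact cancellation.** The 5% rows show what is possible, not what is likely. The argument does not depend on them: pure period and one-way carry-over give the same trigger rate with different bias.
- **The missing period term in the t-tests is immaterial.** With equal orders, period cancels. On the assumed figures, omitting it raises the variance from 16 to 16 + 0.5² = 16.25, about 0.8% on the SE. Adding a position term would leave (Ls − Ln)/2 in the estimate.
- **The direction may not change.** In the pure-period example 2.0, 2.5 and 1.5 all favour the same technique, and the first-sample comparison has z = 2.0/0.376 = 5.3.
- **Details may stand elsewhere.** The full protocol or analysis plan may define the models and the meaning of the conditional presentation. Neither reading of the sentence makes the interaction a suitable condition.

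**Conclusion.** The point holds as a limited one. The article states a data-dependent reporting condition keyed to a contrast, 2P + Ls + Ln, that neither shows nor excludes the bias (Ls − Ln)/2 of the paired comparison. The algebra is exact for the linear models. That period cancels in the paired mean assumes near-equal numbers per order among the analysed children; otherwise P × (n1 − n2)/N remains. The trigger rates and SEs rest on the assumed SD, correlation and effect sizes, since the article gives none.

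It concerns pain, satisfaction and time, and by extension the complication-type outcomes. All are secondary and declared exploratory. A reader might infer that the crossover comparison as a whole, or the primary result, is unsound. The document does not support that: the agreement proportion and its sample size do not depend on this rule, and the article discloses the possible order effect openly. The change is worth making because comfort is a declared aim and the correction is only wording.

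**What to change.** 1. In Limitations of the protocol, delete the condition that ties the presentation of results to a significant interaction.
2. Keep the paired within-child comparison as the main result for outcomes (b) to (g). A first/second position term may be added, with a note that it does not remove carry-over bias.
3. Pre-specify the comparison of first samples only, between the two randomised orders, as a sensitivity analysis free of carry-over, and report it whatever the interaction test shows.
4. Describe the technique-by-order interaction as period plus summed carry-over, not as a test of carry-over. If results by order are shown, say that each contains the period effect in full.

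The cost is wording only, with no change to recruitment, sample size or procedures. The sensitivity analysis will have an interval about twice as wide as the paired one at an assumed correlation of 0.5, which should be accepted in advance.

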## Data Availability

No data was used for the research described in the article.
